^. Along with administering surveys, smartphone-based applications also enable the collection of data using evidence-based scales and instruments on factors that impact youth mental health along with passive data, such as the number of steps taken or screen time
^
12
^, thus making them an effective medium to better understand young people's social, physical and emotional lives. However, the collection, processing, and use of such data, which is considered highly personal by many individuals, will need to be sensitive to the interests of the young people contributing their data. Very little is known about the factors influencing young peoples’ willingness to participate in such research, and across many domains, participation in remote studies tends to drop off quickly
^
13
^, so understanding the factors that attract and maintain participation are important for the success of such research.

Here we describe the protocol for
*MindKind*, a mixed-methods study to understand the feasibility of developing a global mental health database of digital data collected from young adults using smartphones. We hypothesize that young peoples’ willingness to participate in digital research is influenced by their ability to be involved in how their data is collected, shared, and used. To that end, we will directly test a range of data governance models that promote participant-led open data practices
^
14
^ and two different app-based engagement strategies to identify those that lead to the highest participation. Our two-pronged approach pairs a pilot (quantitative) smartphone-based study with a qualitative study to understand the participatory behaviours, concerns, and desires of young people with respect to mobile mental health research. 

This study is being conducted in three countries: India, South Africa and the United Kingdom (UK), which were chosen for their range of economic, socio-cultural and regulatory landscapes. Throughout the project we centre our work on the voices of young people, by grounding our work in a youth-adult participatory research approach whereby we seek to involve youth stakeholders and researchers as equal partners
^
15
^, including as youth leads employed as members of the study staff, youth panel members, and as research participants. We seek to engage young adults with an interest in mental health as co-researchers and partners throughout the entire process, from design, prototyping, and testing of the study frameworks.

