Research norm (Group B): This option presents current researcher community norms for data use, whereby researchers will be able to download a copy of the data from the databank following strict data security rules. Data may be used, unrestricted, by both commercial and non-commercial researchers.Youth informed democracy with download (Group C): Study participants will vote as described in the Democracy Choice above. Under this model, researchers are allowed to download a copy of the data.Youth informed democracy without download (Group D): Study participants will vote as described in the Democracy Choice above. Under this data governance model, data may only be accessed via a restricted server.

In order to mirror the experience in a typical study, participants will be exposed to an informed consent specific to their data governance model and can choose to either join or not. They will have no exposure to other potential governance models. In quantifying the difference in enrolment rates between participants in each group, we can assess whether democratic determination of access terms improves enrolment (Group C vs Group B), and whether restricting data download additionally improves enrolment (Group D vs Group C). We will also assess the effect of governance models on study engagement and retention (See the Data Analysis Plan Engagement section for details).

*Study design: engagement*

Following enrolment in the study, participants will use the study app to complete daily activities and surveys for the course of the 12-week study (
Figure 2). The study poses questions about four active ingredients (AIs) which have been shown to influence mental health: sleep, body movement/exercise, social connections, and positive activities
^
17
^. Participants will focus on one of these domains in four-week rotations. For example, a participant may receive questions about body movement for weeks one to four, positive activities for weeks five to eight, and social connections for weeks nine to 12. See the “
*Surveys and data collection*” section for more details on the content of these domain surveys.

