**Figure 2. f2:**
[figure not shown]
MindKind app study design. The 12-week study is composed of three, four-week rotations focusing on four active ingredients influencing mental health (sleep, body movement, social connections and positive experiences). Participants will be randomized into one of two arms: the first of which allows participants to select their AIs of focus and the second of which randomly assigns the AIs to which participants are exposed. In this example, the ARM 1 participant has selected the topics Body movement, Positive activities and Social connections for their topics, while the ARM 2 participant has been randomly assigned to Sleep, Positive activities and Body movement for their 3 AI topics.

In order to understand whether the choice of survey domain impacts a participant’s short- or long-term engagement in the study, we will independently randomize participants into two different arms (in equal proportion). Participants in the first arm select their AI topic at the beginning of weeks one, five, and nine. Participants in the second arm are randomly assigned to their AIs for each of the three, four-week rotations (
Figure 2).

*Recruitment*

The quantitative substudy aims to recruit 4500 young people (1500 from each country) to download the study app, with a minimum of 10% of the 4500 young people recruited having lived experience of anxiety and depression. The sample size was selected based on expected engagement
^
13
^ in order to achieve a program goal of 100 participants per country completing the 12-week study.

Rolling recruitment will begin in the third quarter of 2021. Youth will be recruited in the following ways:

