**Figure 3. f3:**
[figure not shown]
Baseline, daily, and weekly surveys. MindKind is a 12-week study consisting of a baseline survey followed by four-week rotations focusing on a single “active ingredient” (AI). On the seventh day of the week, a long survey is administered consisting of a standard instrument pertaining to the topic of the AI, as well as PHQ-9 and GAD-7. Preliminary testing showed that this weekly survey took 9 minutes on average (range 3 to 22 min). During the remaining days participants receive short questionnaires including a standard mood question and three to five AI-specific questions. Preliminary testing indicated that the daily surveys took no more than 5 minutes to complete (range 30 sec to 5 min). Participants are prompted to journal on one of those days. At the beginning of weeks five and nine, a new AI is presented (Arm 2) or selected by the participant (Arm 1). This design was selected based on feedback from the PYAs and YPAGs to minimize burden to participants while still collecting rich longitudinal data. PYAs and YPAGs were also consulted in the selection of the specific AIs chosen for implementation.

**Surveys and active data collection:** The questions posed to participants throughout the study focus on the interplay between mood and four different AIs (sleep, social connections, body movement or physical activity, and positive activities) (
Figure 2–
Figure 3). Study participants focus on one AI at a time, in four-week rotations. On days one to six of the week, participants are asked a standard mood question:

Pick the response that describes how you felt today:

○Worst ever○Bad mood○Average○Good mood○Best ever

along with a short (three to five item) AI-specific questionnaire (Appendix 2
^
29
^,
*Extended data*). They are also prompted to journal on an AI-specific or general topic on one of those days. On the seventh day, participants are asked to complete a long survey related to their AI topic (Insomnia Severity Index (seven-item)
^
30
^, UCLA Loneliness Scale (three-item)
^
31
^, International Physical Activity Questionnaire (seven-item)
^
32,
33
^, Behavioural Activation for Depression Scale
^
34
^ for the sleep, social connections, body movement and positive activities AIs, respectively), as well as PHQ-9
^
27
^ and GAD-7
^
28
^ to get a deeper understanding of their mood (
Figure 3).

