**Governance acceptability:** This analysis leverages the enrolment rate for Groups B-D to understand the degree to which a governance model that improves usability and access by investigators, affects study enrolment over models that give participants more control (i.e. democratic determination of data terms) and offer better data security (i.e. secure server access only). The outcome variable for this aspect of the substudy is whether or not the prospective participant enrolled (yes/no). A logistic regression to test the effect of the governance model will be fit, adjusting for age, gender, self-reported present or past mental health issues, and site (global model only). The primary comparisons of interest are Group C vs Group B (democracy vs current norms) and Group D vs Group C (server access vs data download). A secondary analysis will test an interaction term between the model and self-reported mental health issues.

**Engagement:** The goal of this portion of the study is to understand participant engagement and compliance with the study protocol during the course of the 12-week study. We will measure participant engagement based on the following metrics: 1) study completion rates, i.e. proportion of participants that remain active in the study through 12 weeks as well as interim time points (e.g. four and eight weeks); 2) types of data (surveys and passive data streams) shared by participants and for how long; 3) total active tasks completed; 4) time to dropout (i.e. time point of the last task completed).

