For study completion and interim participation, the binary outcome variables ‘participation at time X’ (yes/no) can be modelled using logistic regression to test the effect of the engagement model, adjusting for various socio-demographic factors (e.g. age, gender, self-reported history of mental health challenges), governance model (self-choice, or specific model presented) and site (global model only). For total task completion, the number of tasks completed by a participant will be modelled using Poisson Regression using the same independent variables as previously stated. For assessing the types of data shared by participants, we will compute the aggregate statistics on the number of unique data types shared by participants and for how long. Using a logistic regression model, we will assess the potential differences in data sharing aggregate statistics. Time to dropout can be analysed using a proportional hazards model with censoring at the study end. For each of these three analyses, we will also secondarily examine the effect of the governance model on engagement.

**
*Qualitative substudy*
**

*Study design*

The qualitative substudy aims to (1) identify the consensus data governance model(s) for an open yet privacy-preserving global mental health databank, from the perspective of multinational young people; and (2) understand the concerns, hopes, and expectations of multinational youth for such a databank with regards to the return of value to youth participants and youth participation in databank governance (
Table 2). We will employ a deliberative democracy approach for this study
^
18
^. Deliberative democracy is a method for community engagement in the complex ethical issues surrounding emerging technologies for which most people have not yet formed strong opinions. Deliberative democracy is a distinct qualitative research approach, differing from focus groups by the purposeful provision of educational intervention to enrich group discussion. Further, there is an emphasis on discussion leading to iterative revision of opinions as participants integrate new information and others’ perspectives.

We will conduct two rounds of deliberative democracy sessions. In the first round, up to ten cohorts of five to seven participants will be convened per country (approximately 150 total participants). A sample size of n=50 per site is characteristic of deliberative democracy studies
^
36

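### Total tasks completed is modelled by Poisson regression with no allowance for over-dispersion, so model-based standard errors would be about 1.7 to 6 times too small

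*Protocol article*

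**What the plan says.** The Engagement part of the Data analysis plan lists four metrics, one of which is "3) total active tasks completed". For that metric, "the number of tasks completed by a participant will be modelled using Poisson Regression using the same independent variables as previously stated". Those variables are the engagement arm, socio-demographic factors such as age, gender and mental health history, the governance model, and site in the global model. The same part adds a secondary look at governance effects on engagement. The opening of the Data analysis plan repeats all analyses within site and across sites, with a sensitivity analysis excluding South Africa.

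Three other places determine how the counts will be spread:

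- **Task schedule.** Under Study design: engagement, "participants will use the study app to complete daily activities and surveys for the course of the 12-week study". Under Surveys and active data collection, days one to six carry a short questionnaire, and "On the seventh day, participants are asked to complete a long survey related to their AI topic".
- **Retention.** Under Recruitment, the quantitative substudy "aims to recruit 4500 young people (1500 from each country) to download the study app". That number was chosen from expected engagement "in order to achieve a program goal of 100 participants per country completing the 12-week study".
- **Dropout pattern.** The Introduction says that "participation in remote studies tends to drop off quickly".

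The article nowhere mentions over-dispersion, robust or scaled standard errors, a negative binomial model, or an exposure offset.

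**The concern.** Model-based Poisson standard errors are right only if, given the covariates, the variance of the count equals its mean. A person's completed tasks are not independent events. Someone who leaves in the first week contributes a handful, and someone who stays contributes dozens. Most of the spread in the totals comes from when people stop, and the listed covariates are unlikely to explain much of that.

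If the excess variance is ignored, the rate ratio is still estimated sensibly but its confidence interval is too narrow and its p-value too small. A chance difference between Arm 1 and Arm 2, or between governance groups, could then be reported as an effect of topic choice or governance on engagement. The same error would recur in each within-site, cross-site and sensitivity analysis of this metric. The Discussion says the findings will inform a larger databank.

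**Working it through.** **The plan's own figures.** 3 × 1500 = 4500 recruited, and 3 × 100 = 300 completers. Implied 12-week retention is 100/1500 = 6.7%. This is a retention goal, not a power calculation. Scheduled surveys number 12 × 7 = 84 per person, before baseline sections and journal prompts.

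**Assumptions, because the article does not give them.** A two-sided 5% test; the shape of the dropout curve; and the probability p that an active participant completes a given day's task. Dropout was taken as early (Weibull shape 0.5), constant hazard, uniform, or late (Weibull shape 2). The first, second and fourth curves, and the uniform one, were each set so that 6.7% are still active at day 84.

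**Formulas.** Let T be days active (0 to 84), and let tasks Y be Binomial(T, p).

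- Mean of Y = p × mean(T).
- Variance of Y = p(1 − p) × mean(T) + p² × var(T).
- φ = variance/mean of Y = (1 − p) + p × φ_T, where φ_T = var(T)/mean(T).
- Model-based Poisson standard errors are too small by a factor √φ.
- Actual rejection rate under the null = 2 × [1 − Φ(1.96/√φ)].

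**Worked example, constant hazard.** Mean(T) = 28.5 and var(T) = 614, so φ_T = 21.5. At p = 0.4, φ = 0.6 + 0.4 × 21.5 = 9.2 and √φ = 3.04. The rejection rate is 2 × [1 − Φ(1.96/3.04)] = 52%.

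**Results at 6.7% retention** (φ; standard-error factor √φ; null rejection rate):

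| Dropout | p = 1 | p = 0.7 | p = 0.4 | p = 0.2 |
|---|---|---|---|---|
| Early | 36.3; 6.03; 74% | 25.7; 5.07; 70% | 15.1; 3.89; 61% | 8.1; 2.84; 49% |
| Constant | 21.5; 4.64; 67% | 15.4; 3.93; 62% | 9.2; 3.04; 52% | 5.1; 2.26; 39% |
| Uniform | 14.9; 3.86; 61% | 10.7; 3.28; 55% | 6.6; 2.56; 44% | 3.8; 1.95; 31% |
| Late | 10.7; 3.27; 55% | 7.8; 2.79; 48% | 4.9; 2.21; 37% | 2.9; 1.71; 25% |

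The rejection rate passes 50% once φ exceeds 8.4.

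**Sensitivity.**

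- Counting only the 12 weekly surveys gives φ of 3.5 (constant) to 5.8 (early), and rejection of 29% to 42%.
- If retention were 20% or 40%, with p at least 0.4, φ would be 3.9 to 35 and rejection 32% to 74%. The mildest case run (40% retention, late dropout, p = 0.2) gives φ = 2.4 and 21%.
- To bring φ down to 1, the covariates would have to explain a share 1 − 1/φ of the variance. That is 1 − 1/2.9 = 66% in the mildest cell of the table and 1 − 1/36.3 = 97% in the most severe.

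**Simulation check.** For constant and early dropout with p = 1, 0.7 and 0.4, 1000 null trials per scenario were fitted by Poisson regression on arm, age, gender, mental health history, governance and site, at N = 4500 and N = 1500. Model-based standard errors were 3.0 to 5.9 times too small and rejected 51% to 77% of the time. On the same mean model, robust and quasi-Poisson standard errors rejected 3.9% to 6.2%. The inflation was about the same at both sample sizes, because it depends on φ and not on N. The negative binomial model was not checked in this way.

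**The case against.** **The variance estimator is not stated.** The sentence names a regression family and covariates. Poisson regression with sandwich errors is still Poisson regression, and an unseen analysis plan may specify it. A reader might infer that the analysis is invalid whatever is done; the article does not support that, because the failure depends on model-based errors being used. But the sentence commits to the model, whereas the neighbouring sentences on participation and time to dropout only say what is possible, and nothing in the article signals an adjustment. Ordinary Poisson inference is the natural reading.

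**A null effect would usually look significant.** A reader might infer that a false claim is more likely than not. That holds for constant or early dropout with about 40% or more of tasks completed. The Introduction's remark points towards early dropout, but it is qualitative and the article gives no curve or adherence rate. Nor does the article define which active tasks count. Under late dropout, sparse completion or weekly-only counting, the rate is mostly below 50%. A majority of false positives is therefore not established.

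**The 6.7% comes from a goal.** This is correct, and it is labelled here as an inference. The sensitivity figures show that the conclusion does not depend on it.

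**The stakes are limited.** This also stands. Engagement is a secondary aim of a feasibility study, and task count is one of four metrics. The logistic analysis of completion and the proportional hazards analysis of dropout address the same arm contrast without this defect. The enrolment comparisons and the Group A preference analysis are untouched.

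**Conclusion.** The concern holds in a bounded form. As written, the task-count analysis makes no allowance for over-dispersion that the plan's own schedule and retention goal make almost certain. With model-based Poisson standard errors, φ is about 2.9 to 36 at 6.7% retention, the errors are about 1.7 to 6 times too small, and a nominal 5% test rejects a true null about 25% to 75% of the time. The position within that range rests on the assumed dropout shape and task adherence; the presence of serious inflation does not, since even the mildest case run gave 21%.

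The damage is confined to standard errors, intervals and p-values for the task-count contrasts by engagement arm and by governance model. The point estimate is not affected. This should be fixed before analysis, but it does not threaten the study's primary comparisons.

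**What to change.** Add one sentence to the Engagement part of the Data analysis plan. It should keep the log-link mean model, so that the rate ratio keeps its meaning, and state that inference will use robust (sandwich) or quasi-Poisson standard errors, or a negative binomial model, and that model-based Poisson standard errors will not be used. Apply it to every task-count contrast, by engagement arm and by governance model, within site, across sites and in the analysis excluding South Africa. Robust or quasi-Poisson errors are the simplest choice, since both were checked above and held close to 5%.

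If a separate analysis plan already specifies this, only the article's wording needs aligning. No extra data or design change is needed. The cost is confidence intervals wider by the factor √φ, which is the honest width.

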What are youths’ preferences for how researchers access their data?	Participants randomized to governance Group A ( Figure 1) choose their preference.	Facilitated discussion within deliberative democracy sessions of different data governance options.	Led youth panel 3+ rounds of discussions regarding governance model options. For the quant. substudy, the topics of contention were selected for formal testing. In the qual. study, PYAs helped refine the governance model options and convey these options in plain language. PYAs provided granular, ongoing feedback in developing the governance options. Assisted in the adaptation of the educational materials for the qual. subtudy and recorded audio narration. PYAs will facilitate the deliberative democracy sessions and will help develop the analytical framework and analyze data.	Participated in 3+ rounds of feedback collection regarding governance model options in the quantitative and qualitative substudies. For the quant. substudy, the topics of contention were selected for formal testing. In the qual. substudy, they helped refine the governance model options, convey these options in plain language, and served as mock participants. Will review and provide feedback on the analytical findings of the study upon study completion.	Contributed to scoping and defining the governance model options. In the qual. substudy, DUAG members’ feedback contributed to the advantages and disadvantages of governance models presented in the substudies. Provided input on equity of data access, particularly for less resourced settings.
What are youths’ preferences for who controls access to their data?	Participants randomized to governance Group A ( Figure 1) choose their preference.	Direct inquiry within deliberative democracy sessions.			
Does data governance model affect enrollment or engagement with the app?	Comparison of enrollment rate and engagement for participants randomized to governance Groups B, C & D ( Figure 1).	NA			
Identify the consensus data governance model(s) for an open yet privacy-preserving global mental health databank, from the perspective of multinational young people.	NA	Consensus-building deliberative democracy sessions.	Facilitate qualitative data collection around the research question.	Contribute to early scoping on which data governance model(s) would be presented.	Contributed perspectives on preferred data governance models during study design phase.

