### MindKind study design

To participate in the MindKind study, youth participants must live in one of the participating countries and be legally able to provide consent (age 16–24 in the UK or 18–24 for India and South Africa). Youth are eligible if they can follow study instructions, read and understand English, and have access to an Android mobile phone (for quantitative substudy participation only).

**
*Quantitative substudy*
**

The quantitative substudy is designed to assess the preference and acceptability of different data governance models and their effect on engagement patterns over time. Secondarily, it is designed to test whether choice of study topic affects study engagement (
Table 2).

*Study design: governance models*

 Given the sensitivity of mental health data, we are seeking to understand whether prospective participants of a future global mental health databank have a preference for data governance models which give participants more control over who can access the data and for what purpose. We will also seek to understand whether these preferences impact enrolment. In order to assess these questions, youth participants will be randomized, in equal proportions, to one of four different governance experiences (
Figure 1), the first of which (Group A) assesses preference, with the remaining three (Groups B, C, D) addressing acceptability of various data governance models.

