**Figure 1. f1:**
[figure not shown]
Governance study design. Potential quantitative substudy participants are randomly assigned to one of four consent models. Group A is designed to assess what practices are preferable to study participants. Groups B-D are designed to assess the acceptability of current standards relative to models that allow participants a greater voice and more data security.

In order to assess the preference of young people with regards to data governance, participants randomized to Group A will be prompted to select how researchers are allowed to access their data, and who controls access to the data. The selection of these options was informed by the disparate preferences expressed by youth co-researchers versus the DUAG.

Choice 1: How should researchers be allowed to access the study data?

1.Researchers should be allowed to download a copy.2.Researchers should only be allowed to access the data in a secure server.3.Researchers should only be allowed to see a recreated data set, not the real data. If researchers want to study the real data set, they have to ask the data steward to run their analysis for them. The steward only gives the researcher back the result, not the data.

Choice 2: Who controls the data?

1.Democracy: study participants who select this option get to vote on how the data is used, and the most popular terms are applied to all data regardless of how an individual votes. The results of the vote are shared with participants before data are shared. Any participant who disagrees with the vote may withdraw from the study. See Appendix 1
^
22
^ (

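### The planned effect of governance model on engagement compares enrolees only, although governance is randomised before consent and expected to change who enrols, so it is not a randomised comparison and can be biased in either direction

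*Protocol article*

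**What the plan says.** **Randomisation comes before consent.** The Figure 1 caption states: "Potential quantitative substudy participants are randomly assigned to one of four consent models". The MindKind study design section gives the allocation: "youth participants will be randomized, in equal proportions, to one of four different governance experiences". Under Study design: governance models, "participants will be exposed to an informed consent specific to their data governance model and can choose to either join or not".

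**Enrolment is an outcome.** The Governance acceptability analysis models enrolment (yes/no) in prospective participants. Its main contrasts are C vs B and D vs C, and the design section presents both as tests of whether enrolment improves.

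**Engagement follows enrolment.** Under Study design: engagement, "Following enrolment in the study, participants will use the study app to complete daily activities and surveys". Under Technical implementation, the prompt to download the app comes once a person has enrolled. The engagement metrics are remaining active to 12 weeks, data types shared, tasks completed, and time of the last task.

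**Governance is then compared on engagement.** Table 2 plans a "Comparison of enrollment rate and engagement for participants randomized to governance Groups B, C & D". The design section adds: "We will also assess the effect of governance models on study engagement and retention". The Engagement section closes with "For each of these three analyses, we will also secondarily examine the effect of the governance model on engagement". The named covariates are socio-demographic (age, gender and mental health history as examples), with governance model and site.

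**The concern.** Randomisation makes Groups B, C and D comparable as approached, before anyone has seen a consent form. If one model persuades people to join who would decline another, the enrolees in the two groups are different mixtures. A difference in their engagement then reflects who joined as well as what the model did to them, and the analysis cannot separate the two. The listed covariates do not measure motivation or concern about privacy, which could plausibly drive both joining and staying. The article does discuss bias in the enrolment and engagement analyses, but the only source it names is payment in South Africa.

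At stake is the reading of a stated research question, namely whether the governance model affects enrolment or engagement with the app. A result presented as an effect of the model could arise when the model changes nobody's behaviour after enrolment.

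**Working it through.** **Which people the engagement metrics cover.** The article uses prospective participants for the enrolment outcome and participants for engagement. Remaining active in the study presupposes having joined it, and a person who never received the app has no last task. No denominator that includes non-enrolees is given. The enrolee-only reading is therefore an inference, though a firm one.

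**Inputs.** From the Recruitment section: 1500 people per country downloading the app (3 × 1500 = 4500, which agrees with the stated total) and a goal of 100 completers per country, so completion is 100/1500 = 6.67%. The article gives no enrolment rates and no figure for how the additional enrolees would engage. Those below are assumptions.

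**Formulas.** Let eB and eC be the enrolment rates, pA the completion rate in people who would enrol under either model, pM the rate in people who enrol only under C, and d any true effect of C on the first set. Assume that everyone who would enrol under B would also enrol under C.

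- Enrolees in C: [eB(pA + d) + (eC − eB)pM] / eC. Enrolees in B: pA.
- Per person randomised: enrolment rate × completion among enrolees.

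**Main illustration** (eB 40%, eC 50%, pM half of 6.67% = 3.33%, d = 0):

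- Enrolees in C: (0.40 × 0.0667 + 0.10 × 0.0333) / 0.50 = 0.0600, against 0.0667 in B.
- Odds ratio: (0.0600/0.9400) / (0.0667/0.9333) = 0.89.
- Per person randomised: B 0.40 × 0.0667 = 2.67%; C 0.50 × 0.0600 = 3.00%.
- The ratio of enrolee rates, (0.40 + 0.10 × 0.5)/0.50 = 0.90, does not depend on the 6.67%.

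**Direction** (same enrolment rates, d = 0):

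| pM | Enrolees, B vs C | Odds ratio | Per person randomised, B vs C |
|---|---|---|---|
| 3.33% | 6.67% vs 6.00% | 0.89 | 2.67% vs 3.00% |
| 6.67% | 6.67% vs 6.67% | 1.00 | 2.67% vs 3.33% |
| 10% | 6.67% vs 7.33% | 1.11 | 2.67% vs 3.67% |

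**Range over assumed enrolment rates** (C minus B among enrolees, d = 0). The difference equals [(eC − eB)/eC] × (pM − pA):

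| Enrolment B/C | pM = 2% | pM = 10% |
|---|---|---|
| 40/45% | −0.52 point | +0.37 point |
| 50/60% | −0.78 point | +0.56 point |
| 50/70% | −1.33 points | +0.95 point |
| 70/75% | −0.31 point | +0.22 point |

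**When the sign is wrong.** A true benefit d is hidden or reversed if it is below (eC − eB)(pA − pM)/eB. At 50/60% and pM 2% this is 0.10 × 0.0467/0.50 = 0.93 point. With d = +0.5 point, enrolees in C show (0.50 × 0.0717 + 0.10 × 0.02)/0.60 = 6.31% against 6.67% in B, the wrong sign. Per person randomised the figures are 3.78% vs 3.33%.

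**Chance of a spurious finding.** With 4500/4 = 1125 enrolees per group (an assumption) and a two-sided 5% test (also assumed), the spurious difference at pM 2% is significant in about 12% of trials at 50/60% and 26% at 50/70%.

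**Does covariate adjustment remove it?** In a simulation, an unmeasured trait drove both enrolment and completion, and the model adjusted for a measured covariate. With enrolment of about 50% vs 68% and no effect on completion, the adjusted odds ratio among enrolees averaged 0.82. With no effect on enrolment either, it averaged 1.00.

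**The case against.** **It is secondary, and the main result is sound.** This stands. The Engagement section calls the examination secondary, the study is a feasibility study, and the enrolment contrasts use everyone randomised. No decision rule rests on engagement alone, and a reader given both the enrolment rate and enrolee completion could multiply them. Against that, the opening of the Quantitative substudy section names governance effects on engagement patterns among its design aims, so the wording is worth correcting.

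**The direction is unknown.** This stands. A reader might infer that the better a model recruits, the worse its engagement will look. The documents do not support that. People who join only when offered a vote could be more invested, and the table above then shows an upward bias.

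**The sizes are assumed.** This stands for enrolment and selection. The 6.67% is also per app download, a step after enrolment. In the main illustration the gap is 0.7 point, which 1125 per group would flag in only about 10% of trials.

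**The analysis set may be defined elsewhere.** This stands in part. The Engagement section names no set, and Table 2 speaks loosely of those randomised. But the metric definitions and the causal wording are in the article itself.

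**Counting non-enrolees as zero has its own problem.** This stands. A reader might infer that the all-randomised analysis should replace the enrolee comparison as the governance effect on engagement. In the main illustration nobody's engagement changes, yet that analysis gives 3.0% vs 2.7%. It measures overall participation and must be named so.

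**Covariates are missing for non-enrolees.** This does not stand for the main ones. The Governance acceptability model already adjusts enrolment for age, gender and mental health history, so it needs these for people who decline.

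**Conclusion.** The point holds in a limited form. As described, the governance effect on engagement conditions on enrolment, which is randomised governance's own outcome, so randomisation does not protect it. Bias needs two things: governance must change enrolment, and the additional enrolees must differ in engagement beyond the adjusted covariates. If either fails, the bias is zero.

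If both hold, the assumed ranges above give a spurious completion difference among enrolees of −1.33 to +0.95 points on a base of 6.67%. A modest true benefit could appear with the wrong sign if the additional enrolees are less engaged. These sizes rest on assumed enrolment and selection rates.

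The enrolment comparison is unaffected. So is Arm 1 vs Arm 2, provided that randomisation takes place at or after enrolment. Because the analysis is secondary, this is a should-fix point.

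**What to change.** 1. For C vs B and D vs C, add an analysis of everyone randomised. Count non-enrolees as not participating at weeks 4, 8 and 12 and as having completed zero tasks. Report it as participation (data yield) per person randomised, which is the randomised estimate of governance on overall participation.
2. Keep the enrolee-only comparisons of completion, task count and time to dropout. Describe them as conditional on enrolment, with a selection caveat, and not as a causal effect of the governance model.
3. Leave the Arm 1 vs Arm 2 analyses on enrolees, and state when that randomisation occurs.

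**Cost.** No new data are needed: enrolment status is already an outcome for Groups B to D. The all-randomised estimate combines enrolment with engagement, so it must be labelled as such and read beside the enrolment rate. The Poisson task-count model must allow for the added zeros, for example with robust standard errors.
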